## Abstract

**Background:**

The increase in the survival of oncology patients include multiple side effects as cancer-related asthenia and dyspnea, which represents a serious health problem. An implementation of the conventional clinical practice, developed through multimodal physical exercise and functional rehabilitation program intervention, may be useful in controlling dyspnoea. This study aims to evaluate the effects of a multimodal exercise and functional rehabilitation program on fatigue, pain, functional capacity, and quality of life in cancer patients with cancer-related asthenia.

**Methods:**

This is a protocol for an experimental, prospective, randomised study using a parallel, fixed assignment scheme, with an experimental group and a control group in patients from the oncology hospitalisation unit at the Salamanca University Hospital Complex in Spain, using consecutive sampling to select 50 participants with oncological asthenia who are hospitalised at the time of inclusion. After the baseline evaluation, the participants will be randomised into two groups. Both groups will receive standard clinical practice care and the normal health education program at discharge, but in addition, the participants assigned to the experimental group will also complete a multimodal exercise and functional rehabilitation program lasting one month. The primary outcomes will be basic activities of daily living (Barthel Index) and degree of asthenia (FACT-An scale). Additionally, physical performance will be evaluated with the Short Physical Performance Battery (SPPB), as will the attention and executive functions (Trail-Making Test), fear/avoidance of movement (TAMPA scale), pain (VAS scale), and body composition (waist, hip, brachial, thigh, wrist, and ankle circumferences).

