## Methods/design

### Design and aims

This experimental, prospective, randomized, parallel-controlled clinical trial, with two arms of fixed assignment with an experimental and a control group, will be conducted during a year in the Oncology Hospitalisation Unit at the CAUSA. We will use consecutive sampling to select the participants with oncological asthenia who are hospitalised at the time of inclusion.

This is one of the clinical trials that are starting in our Unit, with an interdisciplinary care team, and similar design, patients and procedures with others, such us the recent study protocol published [19].

According to the background, the primary aim of this study is to assess the effects of a multimodal physical exercise and functional rehabilitation program on fatigue, pain, functional capacity, and quality of life in cancer patients with cancer-related asthenia. The objectives are focused to compare the effects produced by the implementation of a multimodal physical exercise and functional rehabilitation program, with an isolated intervention using standard clinical practice treatment.

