**Fig. 1 Fig1:**
[figure not shown]
Study design. The enrolled participants will be randomly assigned to one of the study groups and will be assessed at three pre-specified time p

We will employ a simple randomisation process that consists of generating a table of random numbers of the same size as the estimated study sample with Microsoft Excel 2020 to assign subjects to each of the study groups. For even numbers, the subject will be assigned to the Experimental Group, and for odd numbers, the subject will be assigned to the Control Group. Randomisation, recruitment and assignment of subjects to each group will be performed by research staff not involved in the evaluations or interventions in each group, which will avoid potential bias in the study.

The participating subjects will not be blinded, due to the specific characteristics of the intervention in each group. However, the researchers responsible for the study measurements and statistical analysis will be blinded, with the intention of avoiding any contamination between groups, thus increasing the rigour of the study process.

Sample size: The sample size has been estimated based on the potential modification of one of the main outcome of the study—the score on the Barthel Index. For this calculation, we have considered the results obtained in a similar, where a modification of 17 points in the BI score was obtained, as a difference attributable to the intervention, considering this as the difference between the modification of the experimental group and the control group [20]. With these premises, accepting an alpha risk of 0.05 and a beta risk of 0.2 in a bilateral contrast, with 50 individuals (25 subjects in the experimental group and 25 in the control group, the statistical power was 90 % to recognize as statistically significant a change of 17 points between both groups in the BI score. The sample size was estimated using the programme EPIDAT 4.2.

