#### Description of the variables

The main variable will be the degree of dependence in performing the activities of daily living (ADL), as measured using the Barthel Index. The secondary variables will be cancer-related asthenia, attention and cognitive functions, health-related quality of life (HRQoL), pain, functional capacity, fear/avoidance of movement using the Tampa Scale for Kinesiophobia associated with Fatigue (TSK-F), and body composition. We will also record the following intervening variables from the patient clinical history: pathological diagnosis, number of treatment lines, and other sociodemographic and anthropometric data.

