#### Tools employed in the evaluation of the variables

“Barthel Index, (BI)” [21]: to evaluate dependence. Measures physical disability with proven validity and reliability. It is easy to apply and to interpret. Useful for evaluating the patient’s functional independence in the activities of daily living (ADL). Scored from 0 to 100, it quantifies the individual’s degree of dependence.“4th version of the Functional Evaluation of Cancer Therapy-Anaemia (FACT-An)” [22]: to evaluate cancer-related asthenia and the functional capacity. The FACT-An scale comprises the FACT-G fatigue subscale, plus seven non-fatigue items related to anaemia in cancer patients. In this study, we will use the version of FACT-G for cancer-related fatigue.“Trail-Making Test (TMT)” [23]: to evaluate attention and executive functions. Useful for to assess attention, flexibility of thinking, and visuospatial ability. The global TMT comprises two parts: the TMT A measures attention, and the TMT B assesses processing speed and executive functions.“EuroQol 5-D Questionnaire (EQ-5D)” [24]: to assess the health-related quality of life (HRQoL). It has been adapted and validated for use in the Spanish population.“A Visual Analogue Scale (VAS)” [25, 26], to evaluate the pain. This will be assessed using the VAS as the most widely used pain assessment scale pain intensity is represented on a 10 cm line where 0 indicates the absence of pain and 10 represents the worst pain imaginable. The patient indicates the intensity of their pain; values less than 4 mean mild or mild–moderate pain; 4–6 indicate moderate–severe pain; and greater than 6 implies very intense pain.“Short Physical Performance Battery (SPPB)” [27]: to evaluate Functional capacity. This test has been validated in the Spanish population for primary healthcare, and was specifically designed to predict disabilities, combines balance, gait speed, and the ability to get up from a chair and has been shown to predict adverse events, dependency, institutionalisation, and mortality.The “Tampa Scale of Kinesiophobia–Fatigue (TSK-F)” [18, 28], was developed to evaluate the fear of movement related to fatigue/pain. It has been proven effective in oncology patients and those with chronic fatigue syndrome. We will use the model with 11 items (TSK-F-11).Evaluation of body composition: by measuring the waist, hip, brachial, thigh, wrist, and ankle circumferences. Height and weight will be measured using a portable stadiometer (Seca, 222), calculating the average of two recorded measurements.

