### Data analysis

The statistical analysis will be carried out on an intention-to-treat basis. The characteristics of the population will be presented as means and standard deviations for continuous variables and as a frequency distribution for qualitative variables. To assess comparability of the two study groups at the baseline, the means between both groups will be compared using chi-square tests for qualitative variables and Student t-tests for qualitative variables. The effect of the intervention on the study variables will be evaluated using a repeated measures ANOVA with two study factors: time * group. Subgroup analyses will be carried out considering certain variables and/or categories from the baseline evaluation such as age or the initial FACT scale score. For hypothesis testing, an alpha risk of 0.05 will be set as the limit for tests of statistical significance. We will use SPSS software (version 23.0; IBM Corp., Armonk, NY) for all the statistical analyses.

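### Asthenia (FACT-An) is a primary outcome in the abstract and a secondary variable in the methods, and its score is named in two ways, so the primary outcome is not fixed

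*Protocol article*

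**What the plan says.** All references are to the protocol article.

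- **Abstract, Methods.** Two primaries: "The primary outcomes will be basic activities of daily living (Barthel Index) and degree of asthenia (FACT-An scale".
- **Description of the variables.** One main variable: "The main variable will be the degree of dependence in performing the activities of daily living (ADL), as measured using the Barthel Index". The next sentence demotes asthenia: "The secondary variables will be cancer-related asthenia", followed by the other secondary domains.
- **Sample/participants, sample size paragraph.** The calculation uses Barthel only, but describes it as "based on the potential modification of one of the main outcome of the study". That wording fits the abstract better than Description of the variables.
- **Tools employed in the evaluation of the variables.** The instrument is introduced as FACT-An, and then: "In this study, we will use the version of FACT-G for cancer-related fatigue".
- **Data analysis.** One repeated measures ANOVA (time by group) serves all study variables, and "an alpha risk of 0.05 will be set as the limit for tests of statistical significance". The section does not say how many outcomes must be positive for the trial to succeed.
- **Design and aims.** The primary aim concerns effects "on fatigue, pain, functional capacity, and quality of life in cancer patients with cancer-related asthenia", without naming activities of daily living.

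**The concern.** The same outcome cannot be both primary and secondary. The Dissemination plan puts the primary results in a first paper and the secondary results in later ones, so the classification decides what leads the report. With the text as it stands, a favourable FACT result could be presented as primary by citing the abstract, and an unfavourable one as secondary by citing the methods. Both choices would be consistent with the published protocol, and both could be made with the data in hand.

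The type I error rate of the primary claim depends on which reading applies. The naming of the FACT score adds a smaller freedom: a reader cannot tell from the article whether the full FACT-An score or a fatigue version tied to FACT-G is meant. FACT has no stated effect size or power under either name.

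**Working it through.** **1. The sections side by side**

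| Section | Barthel Index | Asthenia (FACT) |
|---|---|---|
| Abstract | primary | primary, as FACT-An |
| Sample size paragraph | one of several main outcomes; the only one sized | not mentioned |
| Description of the variables | the main variable | secondary |
| Tools employed | to evaluate dependence | FACT-An, then a FACT-G version for fatigue |

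The abstract and Description of the variables cannot both be right. The sample size paragraph agrees with the abstract in its wording and with Description of the variables in its calculation.

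**2. What the ambiguity does to the error rate**

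Input: 0.05 two-sided for each test (Data analysis; the two-sided contrast comes from the sample size paragraph). Three success rules are possible:

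- *Barthel alone is primary:* error 5%, no adjustment needed.
- *Both must be positive:* error at most 5%, no adjustment needed.
- *Either suffices:* error = 1 − P(|Z1| < 1.96 and |Z2| < 1.96). If independent, 1 − 0.95² = 0.0975. The correlation between the two outcomes is not given, so a range is shown for a bivariate normal:

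| Assumed correlation | 0 | 0.3 | 0.5 | 0.7 | 0.9 |
|---|---|---|---|---|---|
| Familywise error | 9.75% | 9.5% | 9.1% | 8.4% | 7.0% |

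**3. The plan's own power figure**

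Inputs from the sample size paragraph: 25 per arm, difference 17 points, two-sided 0.05. The paragraph gives a beta risk of 0.2 and also a power of 90%. It gives no SD, so the 90% cannot be reproduced. The SD can only be solved backwards:

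SD = 17 / [(1.960 + z_power) × √(2/25)], with √(2/25) = 0.2828.

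- 90% power: 17 / (3.242 × 0.2828) = 18.54 (18.17 with the t distribution).
- 80% power: 17 / (2.802 × 0.2828) = 21.45 (21.02 with the t distribution).

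Both SDs are assumptions.

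**4. The cost of keeping two primaries with alpha split equally (0.025 each, critical value 2.241)**

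Power = Φ[17 / (SD × 0.2828) − 2.241].

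- SD 18.54: Φ(3.242 − 2.241) = Φ(1.001) = 84% (t-based, SD 18.17: 83.6%).
- SD 21.45: Φ(2.802 − 2.241) = Φ(0.561) = 71% (t-based, SD 21.02: 70.6%).

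The number per arm that restores the starting power is n = 2 × (2.241 + z_power)² × SD² / 17².

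- 90% at SD 18.54: 29.5, so 30 per arm, 60 in total.
- 80% at SD 21.45: 30.3, so 31 per arm, 62 in total.

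These totals cover Barthel only. FACT cannot be sized from the article.

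**5. Time point**

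Evaluations and study plan sets assessments at baseline, seven days and hospital discharge. Work plan and visit structure, and the section on follow-up visits, set them at baseline, 15 days and one month. A single primary outcome therefore still lacks a settled time point.

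**The case against.** The strongest reply is that this is a condensed article. Multiplicity rules are commonly left to an analysis plan, which is not shown, and a general significance limit of 0.05 does not say that each primary outcome alone proves efficacy. That stands. A reader might infer that a positive trial can be claimed on either outcome, but no section states such a rule. The article does not exclude it either. The error rates above 5% are therefore conditional, and the absence of an adjustment is not the finding. What the reply does not answer is the contradiction itself: a separate analysis plan cannot make both published classifications of asthenia true.

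Other stronger readings also go further than the text:

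- *A false-positive chance of about 51% across all outcomes.* This comes from 1 − 0.95^14, counting Barthel, FACT, two Trail-Making parts, EQ-5D, pain, SPPB, TSK-F and six circumferences as independent. They are measured in the same patients; at a common correlation of 0.3, 0.5 or 0.7 the figure is 44%, 35% or 25%. Twelve of the 14 are non-primary under both classifications, so the figure does not measure the risk of a false primary claim.
- *The primary aim as a third outcome hierarchy.* The aim does not rank outcomes. It fits poorly with Barthel as the main variable, but that is a matter of wording.
- *A FACT-only result as the least secure because participants are unblinded.* The article does not say how FACT or Barthel is administered, and it does blind those who take the measurements.

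It is also fair to say that the article does not settle which classification was intended: the sample size wording leans towards more than one main outcome.

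**Conclusion.** The point holds as a contradiction in the definition of the primary outcome, together with inconsistent naming of the FACT score. It should be corrected before unblinding, because afterwards the choice could be driven by the results.

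The size depends on the success rule. There is no inflation if Barthel is the sole primary or if both must be positive. If either suffices, the error is 9.75% under independence and between 7.0% and 9.5% for assumed correlations from 0.9 to 0.3. Under an equal alpha split, Barthel power would be about 84% or about 71%, according to whether the SD is the one implied by the stated 90% power or by the stated beta of 0.2. Neither SD is in the article, so neither power is established.

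**What to change.** Make the abstract, the sample size paragraph and Description of the variables name the same primary outcome or outcomes, before unblinding.

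- **Cheapest version.** Barthel Index as the single primary, tested at two-sided 0.05. This matches Description of the variables and the only sample size calculation, and it leaves the total at 50. FACT becomes a secondary outcome, with one named score used in the same words throughout.
- **If both stay primary.** State whether both or either must be positive. If either suffices, split alpha, restate Barthel power with the SD that was used, and give a sample size basis for FACT.
- **In both cases.** State the time point of the primary outcome once the schedule in Evaluations and study plan (discharge) has been reconciled with the one in Work plan and visit structure and the follow-up visits section (one month), and say how the time by group analysis addresses that time point.

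For the outcome definition the cheapest version needs only wording changes. Its price is that the sponsor gives up an efficacy claim on FACT alone. Keeping two primaries with an equal alpha split costs power, or about 10 to 12 more participants for Barthel under the two implied SDs (60 or 62 against 50). Settling the time point is more than an edit, since two schedules are in print.

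### The article gives two primary outcomes in one place and one in another, so the same data could be reported as a positive or a failed primary result

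*Protocol article*

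**What the plan says.** Four places in the protocol article bear on this.

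- **Abstract, Methods:** "The primary outcomes will be basic activities of daily living (Barthel Index) and degree of asthenia (FACT-An scale").
- **Sample/participants, sample size paragraph:** Barthel is "one of the main outcome of the study". The calculation uses Barthel only, "accepting an alpha risk of 0.05 and a beta risk of 0.2 in a bilateral contrast". It takes a between-group difference of 17 points and 25 patients per arm, and states 90% power. No SD is given.
- **Description of the variables**, where the opening sentence reads: "The main variable will be the degree of dependence in performing the activities of daily living (ADL), as measured using the Barthel Index". The next sentence begins: "The secondary variables will be cancer-related asthenia, attention and cognitive functions", followed by the other variables.
- **Data analysis:** the same repeated measures ANOVA (time by group) is applied to the study variables, and "For hypothesis testing, an alpha risk of 0.05 will be set as the limit for tests of statistical significance".

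The section on evaluation tools assigns FACT-An to cancer-related asthenia, so the outcome that is primary in the Abstract is the one that is secondary under the variables.

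**The concern.** The number of primary outcomes fixes what the trial may conclude. Suppose Barthel shows no significant difference and FACT-An gives p<0.05. Under the Abstract, one of two primary outcomes has succeeded. Under the description of the variables, the only primary outcome has failed and FACT-An is a secondary result. As the text stands, the choice between these reports could be made after the results are known. The Dissemination plan puts primary results in a first publication and secondary results in later ones, so the ambiguity also decides what is published first.

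The stated alpha and power belong to the single-outcome reading. With two primaries, either the error rate or the power of the primary claim differs from what the sample size paragraph states, depending on the success rule.

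**Working it through.** **Inputs from the article:** 25 per arm; Barthel difference 17; two-sided alpha 0.05; power stated as 90%, beside a beta of 0.2 in the same sentence.

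**Assumptions, because the article gives no figure:** the SD of Barthel change; the correlation r between the two test statistics (0 to 0.9); the standardised FACT-An effect (0.5 as an example).

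**1. The plan's own power.** Without an SD it cannot be reproduced, only solved backwards. In the normal approximation, SD = 17 / [√(2/25) × (1.96 + z_power)].

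- 90% power: 17 / [0.2828 × (1.960 + 1.282)] = 18.5 (18.2 with the noncentral t).
- 80% power (beta 0.2): 17 / [0.2828 × (1.960 + 0.842)] = 21.5 (21.0 with the noncentral t).

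**2. Reading A: Barthel alone.** Type I error is 5% and the power is as stated. The Abstract and the sample size wording are then wrong.

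**3. Reading B: success on either outcome, each at two-sided 0.05.** With neither effect present, the error is 1 − P(|Z1| ≤ 1.96 and |Z2| ≤ 1.96). For independent tests this is 1 − 0.95² = 0.0975. For correlated tests it comes from the bivariate normal distribution:

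| r | Type I error |
|---|---|
| 0 | 9.75% |
| 0.3 | 9.5% |
| 0.5 | 9.1% |
| 0.7 | 8.3% |
| 0.9 | 7.0% |

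**4. Reading C: both outcomes must succeed.** There is no inflation, but the power changes. FACT-An at a standardised effect of 0.5 with 25 per arm has 41% power (two-sample t-test). With Barthel at 90%, joint power is 0.90 × 0.41 = 37% if independent and about 41% at r = 0.7. It cannot exceed the smaller marginal, 41%. With Barthel at 80% the independent figure is 0.80 × 0.41 = 33%.

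**5. Two primaries with alpha controlled.** Under Holm or an equal split, Barthel may have to be tested at 0.025, with critical value 2.241. Power at that step is Φ(z − 2.241), where z = 1.960 + z_power.

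- 90% premise: Φ(3.242 − 2.241) = Φ(1.00) = 84%.
- Beta 0.2 premise: Φ(2.802 − 2.241) = Φ(0.56) = 71%.

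The noncentral t gives 83.6% and 70.6%. Restoring the original power at 0.025 would need about 30 to 31 per arm.

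Steps 1, 4 and 5 use a two-sample comparison. The planned analysis is a repeated measures ANOVA, so they show scale and do not predict that model's power.

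**The case against.** The strongest reply is that the article condenses a fuller protocol, and that success rules and alpha allocation normally sit in a statistical analysis plan that is not shown. That stands as far as it goes: the absence of a testing order is not in itself an error. It does not cover the contradiction, because the article states two incompatible things about the same outcome.

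A reader might infer that the trial's error rate is in fact nearly doubled. The article does not support that, since no section says success on either outcome is enough. The 9.75% applies only under that reading and with independent tests. FACT-An is described as also covering functional capacity, so some correlation with Barthel is plausible, and correlation lowers the figure. Nor does the 0.05 limit amount to a statement that no adjustment will be made; it is a general threshold.

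A reader might also call FACT-An the riskier route to a claim because participants are not blinded. Barthel is measured in the same participants, and the researchers who take the measurements are to be blinded. The article gives no basis for separating the two outcomes on this ground.

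Two smaller objections stand in part. The phrase in the sample size paragraph is ungrammatical and is weaker evidence than the other two statements. And the primary aim under Design and aims lists fatigue first and does not name Barthel, so which outcome leads is the sponsor's decision.

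**Conclusion.** The contradiction is in the current text and must be resolved, because it decides what counts as success. Each reading requires a correction: to the wording if Barthel governs, to the alpha rule if either outcome suffices, and to the power statement if both are required.

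The size is conditional. Type I error is 5% with Barthel alone, and up to 9.75% if either outcome suffices, falling to 7.0% at a correlation of 0.9. It is not inflated if both must succeed, but joint power would then be about 37% to 41% at a FACT-An effect of 0.5 with Barthel at 90%. The contradiction itself rests on no assumption. The error rates depend on assumed correlations, and the power figures also on a back-solved SD and an assumed FACT-An effect.

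**What to change.** Before unblinding, make the Abstract, the sample size paragraph and the description of the variables agree.

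**Preferred:** the Barthel Index as the sole primary outcome. It is the only outcome the trial is sized on, and the description of the variables already names it. In the Abstract, move FACT-An to key secondary. In the sample size paragraph, call Barthel the main outcome. In Data analysis, add one sentence: Barthel is tested at two-sided 0.05, and FACT-An is tested confirmatorily at 0.05 only if Barthel is significant. This keeps the error over the two outcomes at 5% and costs Barthel no power and no patients.

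**If the sponsor keeps two primary outcomes:** state the success rule and the alpha rule (for example Holm), and restate Barthel power at the 0.025 step. That is about 84% if the 90% premise holds and about 71% if the beta 0.2 premise holds, so the higher figure should not be quoted alone. If both outcomes are required, state the joint power and the FACT-An assumptions behind it.

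**Cost:** a few wording changes and one sentence. Under the preferred option, a FACT-An result alone can no longer be called a primary success. The change may also need notifying to the bioethics committee under the article's section on potential changes.
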